## Abstract

**Background:**

*Vamana* (therapeutic emesis) and *Virechana* (therapeutic purgation) are the two major biopurification procedures enlisted in Ayurveda. Studies explicitly showcasing their clinical efficacy are documented in substantial numbers. *Ritu sodhana* (seasonal purification) imparts rejuvenation in healthy individuals. However, its efficacy for health span and decelerating the aging process in healthy individuals remains a gray area.

**Objective:**

This study’s objective is to explore the effect of *ritu sodhana* on modifying serum levels of malondialdehyde (MDA), total superoxide dismutase (T-SOD), and telomerase activity.

**Methods:**

The study was prospectively registered in the Clinical Trial Registry-India (CTRI; CTRI/2024/02/062176), uses a pre-posttest study design, and includes 53 participants 35 years to 65 years old. The study is exploratory and lacks a control group. Those with a BMI between 18.5 kg/m^2^ and 25 kg/m^2^, with stable weight for 3 months immediately prior to the study, with *madhyama koshta* (medium nature of bowel evacuation, as assessed using aquestionnaire), who are *Vamanarha* (eligible for therapeutic emesis) and *Virechanarha* (eligible for therapeutic purgation), and who do not meet the exclusion criteria will be included in the study. The interventions include emesis in the spring and purgation in the autumn season, preceded by *Snehana* (oleation) and *Swedana* (fomentation) and followed by the *Samsarjana karma* (specialized menu of diets) depending on the measurement of purification. Trial duration will range from 18 days to 20 days for each participant, and the total study duration will be 3 years. The serum levels of MDA, SOD, and telomerase activity will be measured on day 0 and on the next day following completion of the *Samsarjana karma* (18th-20th day). Continuous variables for primary biological endpoints including serum MDA, T-SOD, and telomerase activity will be evaluated using paired-samples *t* tests or Wilcoxon signed-rank tests, with potential missing data managed under a missing completely at random assumption using available case analysis (pairwise deletion) cross-verified by a conservative baseline observation carried forward (BOCF) sensitivity test. The effect size will be also determined.

**Results:**

Recruitment began in March 2025. Data for 27 participants who voluntarily participated in *Vasantha Vamana* were collected in March 2025 and April 2025. Data analysis is pending, and the study is expected to be completed by the end of December 2026.

**Conclusions:**

The study will provide hypothesis-generating evidence, and the data will serve as a necessary precursor to adequately powered, confirmatory trials on the aging process.

## Introduction

### Background

*Vamana* (therapeutic emesis) and *Virechana* (therapeutic purgation) are procedures that help eliminate the accumulated morbid *dosha* (humor) from the body. They are considered the 2 major types of *sodhana* (biopurification) [1]. It has been suggested that “*chirat cha pakam vayasah karoti, samsodhanam samyak upasyamanam*” (ie, body purification delays aging) [2]. Another text says, “*jaram kruchrena labhate chiram jeevatyanamaya*”—a properly administered *sodhana* is able to arrest aging and provide an extended and healthy life span [3].

Retarding the aging process has been considered a target for slowing degenerative diseases. It is also considered a treatment option for tumor suppression. Although the average life expectancy has improved in the last 10 decades, there is no equivalent improvement in healthy life expectancy, which has been termed health span. Data published by the World Health Organization (WHO) in 2019 showed that life expectancy in India was 70.8 years, whereas the health life expectancy was only 60.3 years [4]. Hence, a number of cellular-level and experimental studies are being conducted in this area of research [5,6]. Clinical studies involving humans number the fewest in this area [7].

In a study carried out with 30 healthy volunteers, there was a significant increase in superoxide dismutase (SOD) levels and decrease in malondialdehyde (MDA) levels in the groups administered one 500-mg capsule of *Ashwagandha* and *Guduchi* twice a day for 6 months. The study concluded that *Ashwagandha* and *Guduchi* may be helpful for preventing oxidative stress and premature aging [8]. The results of another study indicated an increase in telomerase activity with no discernible change in telomere length in healthy volunteers aged 45 years to 60 years administered *Amalaki* for 45 days after the *koshta shuddhi* procedure. Telomerase activity and telomere length were analyzed in peripheral blood mononuclear cells on days 0, 45, and 90 of *Amalaki Rasayana* administration. The study concluded that maintenance of telomere length is facilitated by an increase in telomerase activity upon Rasayana administration in older adults and *Amalaki Rasayana* may prevent the erosion of telomeres over a period of time to promote healthy aging in older adults [9]. The randomized controlled trial by Dandekar and Kuchewar [10] investigated the effects of *Vasantik Vamana* karma (therapeutic emesis during spring) on oxidative stress. It found that the procedure significantly reduced MDA levels and increased SOD activity in healthy volunteers. A review on telomerase activators commmeted upon the limited literature on Ayurvedic telomerase activators [11]. The study conducted by Raghuraman and Subramaniam [12] reported a dose-dependent increase in telomerase activity up to 50 μg/mL; after administration, the extract successfully boosted telomerase activity up to a certain dose (50 μg/ml), but adding more than that caused the mixture to become toxic, lowering the cells’ survival rate because the extract did not dissolve properly in the liquid. DLBS1649, a novel extract derived from *Mandukaparni*, was evaluated in lifespan extension studies in fruit flies (*Drosophila*) and showed significant increase in mean survival time in male (>20%) and female (>10%) flies [13].

*Sodhana* can be practiced even by a healthy individual [14]. *Sodhana* offers stability to all bodily tissues, corrects the process of digestion, imparts strength and immunity, favors spermatogenesis and oogenesis, offers relief from diseases, returns an individual to normal physiology, aids with precise sensory perception, enhances mental status, clears the complexion, delays aging, and enables a healthy life span [15]. All these outcomes of *sodhana* are directly opposite to the factors that accelerate the aging process, as per Ayurveda principles. Hence, this study is being conducted to explore the potential of *Vamana* and *Virechana* for decelerating the aging process in healthy volunteers.

### Study Objectives

#### Primary Objective

The primary objective is to evaluate *Vamana* in *Vasanta ritu* (spring season) and *Virechana* in *Sharad ritu* (autumn season) for modulating systemic oxidative stress by measuring the reduction in serum levels of MDA and enhancement of SOD activity from baseline to postintervention.

#### Secondary Objective

The secondary objective is to determine the change in serum telomerase activity from baseline to postintervention.

## Methods

### Trial Design

This open-label, exploratory clinical trial consists of a single group and a primary endpoint of decreasing serum MDA values and increasing serum SOD values within 18 days to 20 days after *Vamana* in *Vasantha ritu* and *Virechana* in *Sarad ritu*. The participants will be recruited by the principal investigator consecutively by season: *Vamana* cohort in the *Vasantha ritu* (spring season) and *Virechana* cohort in the *Sarad ritu* (autumn season). Each participant is enrolled into only one seasonal arm based strictly on their chronological window of voluntary registration. There is no active assignment of participants; instead allocation follows a participant-driven, self-selection framework. The total study duration is 3 years. The study is registered in the Clinical Trial Registry-India (CTRI; CTRI/2024/02/062176).

### Trial Estimand

#### Overview

In accordance with the International Council on Harmonisation (ICH) E9(R1) statistical guidelines, the primary treatment effect targeted for evaluation is precisely defined through a single primary estimand structured across the target population, alternative treatment conditions, primary variables (endpoints), population-level summary measure, and handling of intercurrent events.

#### Target Population

The population consists of healthy adult volunteers aged 35 years to 50 years, residing in Kerala, India, who have been cleared of any baseline noncommunicable diseases (NCDs) or metabolic comorbidities via our 3-tier screening matrix.

#### Alternative Treatment Conditions

This includes the intra-individual pre-intervention baseline status (T₀) compared against the postintervention state (T₁) following the completion of a season-specific, inpatient *Śodhana* (*Vamana* or *Virechana*) and graduated *Samsarjana Krama* package.

#### Primary Variables (Endpoints)

The endpoints consist of continuous laboratory biomarker change scores measuring oxidative stress indicators, specifically MDA and SOD, and cellular longevity parameters, including telomerase activity.

#### Population-Level Summary Measure

The mean intra-individual change score (mean delta difference) will be calculated from baseline to postintervention across the pooled cohort of 53 participants.

#### Handling of Intercurrent Events

Intercurrent events anticipated in this protocol include clinical dropout, voluntary withdrawal, or protocol nonadherence (such as violating the inpatient *Ahara* or *Vihara* constraints). To handle these events, a “While-On-Treatment” strategy will be used. The target estimation focuses strictly on the biological treatment effect achieved while participants successfully adhere to the intensive inpatient intervention. Data points collected up to the exact moment of any protocol violation or withdrawal will be retained, while missing postevent endpoints will be mathematically handled using multiple imputation methods within our multivariable regression models, preventing bias from complete-case attrition.

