### Participant Retention and Discontinuation Protocols

Participant retention is optimized through the fully managed inpatient environment. This trial tracks an existing clinical service where healthy volunteers are admitted as full hospital inpatients for the duration of the *Śodhana* therapy; therefore, typical outpatient compliance barriers like travel issues, appointments being forgotten, or accidental dietary deviations are naturally eliminated.

For participants who voluntarily withdraw or deviate from the intervention protocols after formal enrollment, active procedures are immediately halted to protect participant autonomy and safety. Unless written consent is completely revoked, the specific outcome data collected and retained for these individuals will consist of baseline serum MDA, T-SOD, and telomerase levels, along with a documented record of the exact chronological point and clinical reason for the protocol deviation or study exit. The reasons for nonadherence and nonretention will be recorded on the CRF. All recorded reasons will be compiled into a standardized trial flow diagram and fully disclosed in the final manuscript publication.

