### Statistical Handling of Missing Data

This trial evaluates objective biochemical endpoints within a strictly monitored hospital inpatient setting; the incidence of missing data is anticipated to be extremely low (<5%). Any missing data points are assumed to follow a missing completely at random mechanism, as data omissions would stem strictly from random logistical or laboratory anomalies.

Missing data will be handled using an available case analysis (pairwise deletion) framework for the primary longitudinal comparisons, ensuring that all available valid pairs of pre- and postintervention biochemical metrics are fully utilized without fabricating data. To verify that this approach does not introduce statistical bias, a conservative baseline observation carried forward (BOCF) sensitivity analysis will be executed concurrently. Under the BOCF framework, any missing postintervention value will be replaced by the participant’s own baseline value, assuming zero therapeutic change. This dual-validation approach guarantees a highly transparent, noninflationary evaluation of the trial’s biochemical endpoints.

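### The single primary estimand has contradictory rules for participants who stop: while-on-treatment with multiple imputation in one section, available pairs under MCAR in the others

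*Protocol article*

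**What the plan says.** The Trial Estimand overview announces one primary estimand. Its parts, and the later analysis sections, treat participants who stop as follows.

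- **Summary measure** (Population-Level Summary Measure): the mean change is taken "from baseline to postintervention across the pooled cohort of 53 participants".
- **Events and strategy** (Handling of Intercurrent Events): "Intercurrent events anticipated in this protocol include clinical dropout, voluntary withdrawal, or protocol nonadherence". Then: "To handle these events, a “While-On-Treatment” strategy will be used". For values missing after the event, "missing postevent endpoints will be mathematically handled using multiple imputation methods within our multivariable regression models". The section presents this as protection against the bias of dropping incomplete cases.
- **Primary analysis** (Statistical Handling of Missing Data): "Missing data will be handled using an available case analysis (pairwise deletion) framework for the primary longitudinal comparisons". The assumption is that "Any missing data points are assumed to follow a missing completely at random mechanism", because losses are expected to come only from chance laboratory or logistical failures. Missing data are expected to stay below 5%. The Abstract gives the same rule.
- **Sensitivity** (Sensitivity Analyses): missing or protocol-deviated post-intervention values are replaced by baseline (BOCF). If significance at .05 agrees between the two analyses, the findings are to be declared clear of attrition bias.
- **Data held on stoppers** (Participant Retention and Discontinuation Protocols): procedures halt and "the specific outcome data collected and retained for these individuals will consist of baseline serum MDA, T-SOD, and telomerase levels", plus the time and reason of exit.
- **Measurement times** (Abstract, Methods): day 0 and the day after the dietary phase ends (day 18 to 20), nothing between.
- **Dropout** (Sample Size): 20% is assumed.

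**The concern.** An estimand section should fix what is estimated when a participant stops, and the analysis should then estimate it. Here the two are at odds on the events the protocol itself expects: "clinical dropout, voluntary withdrawal, or protocol nonadherence". The estimand text names one strategy, describes a method that belongs to another, and rejects the analysis that the later sections make primary.

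The MCAR rationale covers lost tubes and failed assays but not withdrawal or nonadherence. Stopping an emesis or purgation regimen may well relate to how the person tolerates or responds to it, so MCAR cannot simply be asserted there.

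Success is judged on P<.05 together with a moderate to large Cohen d (Primary Outcome). An unclear denominator therefore feeds directly into the conclusion. The mean change in completers could be reported as the mean change in everyone enrolled, with a statement that attrition bias has been excluded.

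**Working it through.** **1. The plan's own figures.** Inputs from Sample Size: Z = 1.96, P = 0.5, d = 0.15, dropout 20%.

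- n = 1.96² × 0.5 × 0.5 / 0.15² = 42.68; 42.68 / 0.80 = 53.36. The stated 53 reproduces (54 if rounded up).
- Paired two-sided t test, n = 53, Cohen d = 0.395, alpha .05: power 0.806 against the stated 80%. This also reproduces.

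The point therefore does not rest on a sample-size error. The inputs do give two loss rates. At 20%, 53 × 0.80 = 42.4, so about 42 pairs remain and 11 are lost. Below 5%, at most 2 are lost (2/53 = 3.8%; 3/53 = 5.7%).

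**2. The rules side by side, for someone who stops before the second blood draw.**

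- *While-on-treatment* needs an outcome observed before the event. The only value held is baseline, so there is no on-treatment change.
- *Multiple imputation of the day 18 to 20 value* estimates what would have been seen had the person continued. That is a hypothetical strategy.
- *Available pairs* drop the person. With two time points and a change score, this is a complete-case analysis, and its natural target is the change in completers.
- *BOCF* sets the change to zero, which is a further target.

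**3. Size, if stoppers truly have no change (an assumption).** With k lost, whole-cohort mean = completer mean × (53 − k)/53, so available-pair mean / whole-cohort mean = 53/(53 − k).

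- k = 2: 53/51 = 1.04, about 4% too high.
- k = 11: 53/42 = 1.26, about 26% too high. For example, a completer mean of 0.50 SD corresponds to 0.50 × 42/53 = 0.396 SD in the whole cohort.

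**4. Would imputation remove it?** Illustrative simulation. Assumptions: pre/post correlation 0.5, true mean change 0.395 SD of change, stopping more likely at higher baseline, 4000 runs, regression imputation on baseline.

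- 10 of 53 stop: available pairs 0.486, BOCF 0.395, imputation 0.395.
- 2 of 53 stop: 0.410, 0.394, 0.391.

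When an observed baseline value drives stopping, imputation recovers the true mean. It cannot do so when stopping depends on the unobserved response. BOCF's agreement with the truth is a coincidence of this scenario. If stopping is random, BOCF shrinks the mean to 51/53 = 96% (2 lost) or 43/53 = 81% (10 lost).

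**5. Does agreement in P<.05 exclude attrition bias?** Take d = 0.395 in completers. With a fraction f set to zero, the BOCF mean is (1 − f)d and its variance is (1 − f)(1 + d²) − [(1 − f)d]².

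- 2 lost: power 0.790 (pairs) and 0.788 (BOCF).
- 11 lost: power 0.705 and 0.696, although the BOCF mean is only 42/53 = 79% of the completer mean.

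The two tests have almost the same chance of significance on largely the same data, and neither uses the stoppers' true outcomes. Agreement is to be expected whether or not stoppers differ, so it says nothing about attrition bias.

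**The case against.** **Imputation may be meant only for secondary models.** The estimand section places it in the multivariable regressions, which Statistical Measures introduces as secondary. The Abstract, Statistical Handling of Missing Data and Sensitivity Analyses all agree on available pairs as primary and BOCF as the check. This stands as a fair reading, and it means the analyst is not plainly offered two rival primary analyses. It does not remove the conflict. The imputation rule is stated for the single primary estimand, and on this reading the primary paired test is still the complete-case analysis that the same paragraph says it avoids.

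**The primary result might seem undefined for anyone who stops.** A reader could infer this, but the text does not support it. The missing-data section can be run as written: stoppers leave the paired test and re-enter at zero change under BOCF.

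**Pairs and imputation might both seem to credit stoppers with the completers' benefit, making the bias-prevention claim simply false.** That is too strong. The planned regressions include baseline, age, sex and BMI, and step 4 shows imputation can correct baseline-driven stopping. The supportable criticism is that protection is not guaranteed.

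**The 53 may all be completers.** Expected Completion ends the trial once 53 have finished. If so, the summary measure already describes completers, but Sample Size reaches 53 only after adding 20% for dropout. The text supports both readings.

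**The study is exploratory, inpatient and expects few losses, and BOCF would show the zero-change case.** This stands. It limits the consequence and argues against the highest severity.

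**Conclusion.** The contradiction is in the text and should be fixed before analysis. The named strategy cannot be observed for stoppers with two blood draws and baseline-only retention. The described imputation targets a different, hypothetical quantity, and the primary analysis estimates the change in completers while the summary measure speaks of a pooled 53. MCAR is justified for only one kind of loss, and the 20% and below-5% rates are not reconciled. The inference from matching P values to absence of attrition bias does not follow.

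The overstatement of the whole-cohort mean is about 4% with 2 of 53 lost and about 26% with 11 of 53 lost, assuming stoppers truly have no change. Quoting 26% alone would ignore the protocol's own lower rate. Neither figure is a forecast.

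The analysis is contradictorily specified, not impossible to run. The study is uncontrolled and hypothesis-generating, and the repair leaves the primary computation unchanged, so this is a should-fix point.

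**What to change.** Choose one target and carry it through.

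- **Primary analysis:** keep available T0/T1 pairs as the only primary analysis, and state its target as the mean change in participants who complete the package.
- **Population-Level Summary Measure:** refer to completers, and align this with Expected Completion and Sample Size on whether 53 means enrolled or completed.
- **Handling of Intercurrent Events:** delete the while-on-treatment label, the multiple-imputation sentence and the bias-prevention claim. Alternatively, keep imputation as a sensitivity analysis explicitly labelled as hypothetical (had all completed).
- **Abstract and Statistical Handling of Missing Data:** confine MCAR to laboratory or logistical losses, and reconcile the below-5% expectation with the 20% dropout.
- **Sensitivity Analyses:** keep BOCF as the zero-change case, optionally widened to a range of delta-adjusted values. Delete the statement that agreement in significance shows freedom from attrition bias.
- **Deviators:** reconcile Sensitivity Analyses, which provides for replacing their post-intervention values, with the retention section, which keeps only baseline.
- **Reporting:** give withdrawals by reason and by seasonal cohort.

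The cost is rewording these sections and, if chosen, a short extra sensitivity analysis. No additional samples are needed. The downside is a narrower stated target: the result will describe completers and not everyone who enrols.

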### Statistical Measures

The change in values of the outcome measures including MDA, SOD, telomerase activity, and telomere length will be recorded. The data will be tested for normality using the Shapiro-Wilk test. They will be tested for significance using paired *t* tests (if the data are normally distributed) or the Wilcoxon Signed Rank test (if the data are not normally distributed). A *P* value <.05 will be considered significant. All statistical analysis will be conducted using SPSS version 31 (IBM Corp). Moreover, a secondary exploratory subgroup analysis will be conducted within and between the 2 cohorts (*Vamana* and *Virechana* groups) based on the distribution of the data. If the data are normally distributed, within-group analysis will be conducted using paired *t* tests and between-group analysis will be conducted with *t* tests, whereas Wilcoxon Sign Ranked tests and Mann-Whitney *U* tests will be used, respectively, for data that are not normally distributed.

Cohen *d* effect sizes will also be calculated to address the exploratory nature of the study and evaluate the clinical and biological relevance of changes in biomarkers (ie, MDA, SOD, and telomerase activity). Results will be interpreted based on the magnitude and directionality of these effect sizes (small: 0.2; medium: 0.5; large: 0.8) to provide a standardized measure of treatment impact beyond simple *P* value testing.

Given the exploratory, hypothesis-generating design of this pilot study, secondary multivariable analyses will be introduced to evaluate the influence of potential baseline confounders. For normally distributed continuous data, an analysis of covariance (ANCOVA) will compare postintervention outcomes between the 2 seasonal subcohorts (*Vamana* vs *Virechana*) using individual pre-intervention scores as the baseline covariate to mathematically adjust for initial biological variation. Additionally, to evaluate the entire cohort of 53 participants as a unified group, multiple linear regression models will be constructed using the postintervention scores as the dependent variable, entering baseline biomarker values, age, sex, and baseline BMI as independent predictors to systematically control for demographic and physical confounding variables.

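### Multiple imputation within the stated regression reproduces the complete-case fit, so it cannot prevent attrition bias in the way the estimand section claims

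*Protocol article*

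**What the plan says.** All references are to the protocol article.

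- **Handling of Intercurrent Events** names dropout, withdrawal and nonadherence, adopts a while-on-treatment strategy and states: "Data points collected up to the exact moment of any protocol violation or withdrawal will be retained". It then says: "missing postevent endpoints will be mathematically handled using multiple imputation methods within our multivariable regression models, preventing bias from complete-case attrition". No condition is attached to the last clause.
- **Abstract, Methods** gives two measurement times: "The serum levels of MDA, SOD, and telomerase activity will be measured on day 0 and on the next day following completion of the" dietary phase, that is, day 18-20.
- **Participant Retention and Discontinuation Protocols** says of people who withdraw or deviate that "the specific outcome data collected and retained for these individuals will consist of baseline serum MDA, T-SOD, and telomerase levels", together with the time and reason of exit.
- **Statistical Measures** builds the pooled regression "using the postintervention scores as the dependent variable", "entering baseline biomarker values, age, sex, and baseline BMI as independent predictors".
- **Population-Level Summary Measure** defines the target: "The mean intra-individual change score (mean delta difference) will be calculated from baseline to postintervention across the pooled cohort of 53 participants".
- **Statistical Handling of Missing Data** says: "Missing data will be handled using an available case analysis (pairwise deletion) framework for the primary longitudinal comparisons". It assumes data are missing completely at random, expects under 5% missing, and adds baseline observation carried forward (BOCF) as a sensitivity analysis. Neither it nor **Sensitivity Analyses** mentions multiple imputation.

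**The concern.** The estimand section credits a method with a property. Whether the method has it depends on what is known about the people who leave. Here only the outcome is missing, and every stated predictor is a baseline variable already in the regression. Imputation then has nothing to draw on beyond what the completers' regression already uses.

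At stake is how a single-group pre-post result is read. If people who tolerate the procedure poorly, or respond weakly, leave more often, the estimate is too favourable, and a reader told that attrition bias has been prevented would not look for this. The two sections also do not fit together. If data are missing completely at random, completers carry no attrition bias to prevent. If they are not, pairwise deletion is exposed to it.

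**Working it through.** **1. What is observed.** Write X for intercept, baseline marker, age, sex and BMI, and y for the post score. Completers (o) have X and y. Leavers (m) have X only. No marker is measured between day 0 and day 18-20, so data kept up to the event are baseline data. Time and reason of exit exist only for people without y, so nothing observed links them to y.

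**2. Regression coefficients.** Complete-case fit: b = (X_o'X_o)⁻¹ X_o'y_o. Imputation from the same predictors centres the leavers' values on X_m b. The fit to the completed data is then

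(X_o'X_o + X_m'X_m)⁻¹ (X_o'y_o + X_m'X_m b) = (X_o'X_o + X_m'X_m)⁻¹ (X_o'X_o + X_m'X_m) b = b.

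Only the finite number of imputations separates the two. This does not depend on why people leave.

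**3. Numerical check (simulation B).** n = 53, 1,000 runs, 50 imputations. Assumed, not in the documents: SD 1, pre-post correlation 0.5, mean change -0.395 (the size of the effect in the protocol's power statement). Regression results at 20% leaving:

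| Leaving driven by | Slope: full / complete-case / imputed | Intercept: full / complete-case / imputed |
|---|---|---|
| Baseline | 0.502 / 0.505 / 0.505 | -0.388 / -0.381 / -0.382 |
| Unseen post value | 0.501 / 0.382 / 0.382 | -0.382 / -0.621 / -0.621 |

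The largest coefficient difference between imputed and complete-case averaged about 0.02 with 50 imputations and 0.0023 with 5,000 (five data sets). In the first row there is no bias to remove. In the second it stays in full.

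**4. Mean change over all 53.** Completers' residuals sum to zero, so the imputed mean equals the complete-case regression averaged over everyone's X, minus the mean baseline. This differs from the mean of available pairs. Simulation B:

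| Leaving | Driven by | Full | Available pairs | Imputed | BOCF |
|---|---|---|---|---|---|
| 20% | chance | -0.397 | -0.397 | -0.397 | -0.315 |
| 20% | baseline | -0.392 | -0.243 | -0.390 | -0.192 |
| 20% | post value | -0.392 | -0.540 | -0.633 | -0.428 |
| 5% | baseline | -0.390 | -0.344 | -0.392 | -0.325 |
| 5% | post value | -0.396 | -0.445 | -0.472 | -0.420 |

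Imputation removes baseline-driven bias. It does not remove outcome-driven bias, and here it increases it.

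**5. Size under response-dependent leaving (simulation A).** n = 53, true benefit 0.40 SD of change, 20 imputations, 3,000 runs. The 20% rate is the Sample Size allowance: 1.96² × 0.25 / 0.15² = 42.68, and 42.68 / 0.80 = 53.35, against the stated 53. The log-odds of leaving per SD of response are assumed.

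| Leaving | Mechanism | Available pairs | Standardised complete-case regression | Imputed | Overstatement after imputation |
|---|---|---|---|---|---|
| 20% | response, log-odds 1.0 | 0.58 | 0.55 | 0.55 | 0.55/0.40 - 1 = 38% |
| 20% | response, log-odds 0.5 | 0.50 | 0.48 | 0.48 | 0.48/0.40 - 1 = 20% |
| 5% | response, log-odds 1.0 | 0.45 | 0.44 | 0.44 | 0.44/0.40 - 1 = 10% |
| 20% | baseline only | 0.47 | 0.40 | 0.40 | none |

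**The case against.** A reader might infer that imputation is useless here and removes no attrition bias at all. The documents do not support that. The sentence belongs to an estimand whose summary is the mean change over all 53, and for that mean imputation does correct leaving that depends on baseline (simulation B: -0.243 becomes -0.390, against -0.392). This stands, and it limits the point.

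The equality in step 2 also assumes that the imputation uses only the regression's own predictors. The article does not say so, and the content of an imputation model is commonly left to an analysis plan. Daily adherence, adverse events and rescue events are recorded for completers too, and season is absent from the pooled model. With a predictive auxiliary variable added, simulation B gave an imputed intercept of -0.398, against -0.548 complete-case and -0.397 full data. This stands as a possibility. The article names no such variable, describes adherence tracking as descriptive, and attaches no condition to its claim.

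Response-dependent leaving is an assumption. The listed events do not mention biomarker response, and no participant could leave because of a marker result not yet measured. Poor tolerance is a plausible reason to leave, but its link to the markers is not documented.

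It would also be wrong to infer that the plan has no protection. BOCF is planned, and its mean is the completers' mean times the fraction observed. In simulation A that gives 0.58 × 0.80 = 0.46, 0.50 × 0.80 = 0.40 and 0.45 × 0.95 = 0.43, against a truth of 0.40. That protection comes from BOCF, not from the imputation credited with it.

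Finally, if the conflict is settled in favour of the missing-data section, the sentence goes. If it is settled the other way, the claim is still wrong as written.

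**Conclusion.** The unconditional claim is wrong as written. With only baseline data on leavers and only the stated baseline predictors, imputation within the pooled regression gives the complete-case result and cannot prevent bias from leaving related to tolerance or response. This part is algebra and depends on no assumed correlation or leaving mechanism, only on there being no auxiliary variables. For the mean change, imputation helps to the extent that leaving is explained by the variables in the imputation model. The missing-data section does not use it there.

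The size of any bias is uncertain: about 10% at 5% leaving and 20-38% at 20% leaving, only if leaving depends on response, and other assumptions give other figures. With under 5% missing expected in a supervised inpatient setting, the effect may be small. This is a correction to a stated property and to one analysis choice. It does not show that the trial's result will be biased.

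**What to change.** 1. In Handling of Intercurrent Events, delete the closing clause on preventing bias, or limit it to attrition explained by the variables in the imputation model, and name those variables.
2. Reconcile that section with Statistical Handling of Missing Data and Sensitivity Analyses, so that one method is primary for the mean change and its assumption is stated once.
3. Report the mean change from the already planned regression standardised to the baseline values of all enrolled participants, or the equivalent imputation. This is less biased than pairwise deletion when leaving depends on baseline.
4. Keep BOCF as the check for zero benefit in leavers. Optionally extend it to a small grid of shifts in leavers' imputed values that includes values worse than zero change, and report the shift at which the 95% CI includes zero. State how this check relates to the while-on-treatment strategy.

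The cost is a weaker stated claim and a few more lines of analysis. No new data are needed, and the article reports that data analysis is still pending.
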